### Intervention

The intervention is developed based on Social Cognitive Theory which includes social support, self-regulation and self-efficacy [17]. There will be three main components in the intervention i) Peer support for home blood pressure monitoring, ii) Face to face health coaching on healthy diet iii) Demonstration and training for indoor home based exercise activities.

Peer support groups, consisting of five persons per group will be formed based on the proximity of the residences. An Omron digital blood pressure monitor (HEM-7111) will be distributed to each group and participants will be trained by a state registered nurse on how to measure blood pressure and record the blood pressure reading in a log book.

Dietary assessments of individual participants will be conducted by three dietitians using 7 days diet histories. These dietitians will be randomly assigned to participant groups to assess the food intake. The same principal dietitian will conduct six sessions of health coaching to the participants in the group. The content of health coaching will include diet modification according to the DASH (Dietary Approaches to Stop Hypertension)diet [7,18] and reduction of sodium intake. The sodium reduction approach that will be used in this study is by educating the participants to use herbs and spices in their cooking and by reducing the table salt usage. Healthy cooking demonstration and practices of reading food label will also be included in the sessions of health coaching. High in sodium foods will be encouraged to be minimised. The health coaching materials to the intervention groups are the same whilst control will receive healthy diet leaflet at the beginning of the study. After completing the intervention, the three dietitians will do the post intervention dietary assessment using the 7 days diet histories.

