### Follow up and outcome measurement

The follow up will be at six months and twelve months for both intervention and control groups. The GPAQ questionnaire survey, 7 days diet history, blood pressure measurement and physical evaluation will be conducted at baseline, six months and twelve months. The log book kept by participants in the intervention group will be checked for completeness and errors after one month of the intervention and the record will be taken at three, six, nine and twelve months in order to check the compliance of self-blood pressure monitoring and home-based exercise, and whether they measured their blood pressured once a week or not.

The primary outcomes will be systolic and diastolic blood pressure measured at zero month (enrolment), six months (end of intervention period), and twelve months (maintenance period). Secondary outcome measures include some Social Cognitive Theory variables related to self-efficacy and self-regulatory such as practice of self-blood pressure monitoring, and adherence of exercise. Other secondary outcomes will be dietary intake, level of physical activity and physical fitness in term of both cardio vascular endurance and muscle strength.

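### The Intervention section permits, and its wording suggests, that the dietitian who coaches intervention participants also takes their outcome diet histories, which exposes the dietary secondary outcomes to a bias in one arm

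*Protocol article*

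**What the plan says.** Four statements in the Intervention section of the protocol article set the arrangement:

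- Who assesses: "Dietary assessments of individual participants will be conducted by three dietitians using 7 days diet histories".
- How assessors are assigned: "These dietitians will be randomly assigned to participant groups to assess the food intake".
- Who coaches, in the sentence that follows directly: "The same principal dietitian will conduct six sessions of health coaching to the participants in the group". The sessions cover the DASH diet and sodium reduction.
- Who assesses at the end: "After completing the intervention, the three dietitians will do the post intervention dietary assessment using the 7 days diet histories".

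The same section confines the coaching to one arm: "The health coaching materials to the intervention groups are the same whilst control will receive healthy diet leaflet at the beginning of the study". Study design and setting describes the trial as un-blinded. Dietary assessment says that trained dietitians conduct the diet history, with a flip chart to help estimate portions. Follow up and outcome measurement schedules it at baseline, six and twelve months and lists it as a secondary outcome: "Other secondary outcomes will be dietary intake".

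**The concern.** A diet history is a self-report drawn out by an interviewer. The respondent can shade the answers, and the interviewer can probe or estimate portions differently. If the interviewer is also the person who spent six sessions advising less salt and a different diet, both tendencies push towards apparent adherence. Controls receive a leaflet and have no coach, so there is no matching push in their arm.

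Diet is one of the routes by which the intervention is meant to lower blood pressure, and it is named in the objectives. A reporting shift confined to the coached arm could appear as a significant dietary improvement when intake has not changed. It could then be read as support for the mechanism. If every coached participant were assessed by the coach, no later analysis could separate this shift from a real effect, because it would coincide with treatment.

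**Working it through.** The plan gives no figure on this point. The check is first a reading of the text, then an illustration of size.

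**Reading the text.** The only dietitians introduced before the coaching sentence are the three assessors, and the group in that sentence most readily refers back to the groups to which they were assigned. Three readings are possible:

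1. Each group's assigned assessor becomes its coach. If assessors keep their groups, every coached participant reports to his or her coach.
2. One lead dietitian, who is one of the three, coaches everyone. Part of the coached arm then reports to the coach.
3. One lead dietitian from outside the three coaches everyone. No participant reports to the coach.

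The text rules out none of these. Its order and the word linking coach to assessor favour an overlap (1 or 2).

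**Does analysing change remove it?** Data management and analysis compares change in blood pressure and says that secondary outcomes are examined in the same way. Stable differences between dietitians largely cancel in a change score if the participant keeps the same dietitian. A shift that begins with the coaching is absent at baseline and present at follow-up, so it does not cancel.

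**Illustration of size.** Inputs:

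- 160 per arm and 30% dropout (Sample size calculation and recruitment): 160 × 0.70 = 112 completers per arm.
- 5% significance level, taken as two-sided.
- True dietary effect zero; clustering ignored.
- Reporting shift b, in SD units, in the coached arm only. The documents give no value, so b is an assumption.

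Standard error of the difference in SD units: √(2/112) = 0.1336.

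Rejection rate = 1 − Φ(1.96 − b/0.1336) + Φ(−1.96 − b/0.1336).

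- b = 0: 5.0%.
- b = 0.10: b/SE = 0.748; 1 − Φ(1.212) + Φ(−2.708) = 0.113 + 0.003 = 11.6%.
- b = 0.20: b/SE = 1.497; 1 − Φ(0.463) + Φ(−3.457) = 0.322 + 0.000 = 32.2%.

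With all 160 per arm retained, the same formula gives 14.5% and 43.2%.

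**Dilution under reading 2.** Suppose the lead coach takes one third of the coached arm's histories (an equal split among three, also an assumption). A shift of 0.20 SD in that third averages 0.20/3 = 0.067 SD over the arm. Then b/SE = 0.499 and the rate is 1 − Φ(1.461) + Φ(−2.459) = 0.072 + 0.007 = 7.9%. A shift of 0.10 SD averages 0.033 SD and gives 5.7%. Under reading 3 the coach contributes no shift.

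**The case against.** **The overlap is inferred.** This stands. The coach is described in the singular and as the principal dietitian, which may mean a lead from outside the three. A reader might infer that the protocol has the coach assess his or her own participants; it permits and suggests this but does not state it.

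**A condensed article leaves assessor rotas to the full protocol.** This stands only in part. Silence on a rota would be no finding. Here, however, the article itself states who assesses, who coaches and who returns to assess, and the point concerns what those statements set up together.

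**Random assignment of assessors.** A reader might also infer that assigning three dietitians by participant group itself biases one arm. The documents do not support that. Random assignment has no expected direction. The only groups given a size are the peer groups: "Peer support groups, consisting of five persons per group will be formed based on the proximity of the residences". At 160/5 = 32 such groups in the intervention arm, a badly uneven spread of three dietitians is unlikely. The unit of assignment is unclear, since peer groups are described only within the intervention, but it is not shown to be wrong. Random assignment nevertheless does nothing about bias that comes from coaching.

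**The shift is assumed and would partly persist.** Both parts stand. Participants know their arm and what they were taught, so some desirability bias would remain with any interviewer. Separating the roles removes only the part due to the coach asking and recording.

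**Standardisation.** Trained dietitians, a pre-tested tool and the flip chart reduce differences in technique. They do not alter what a participant chooses to tell the coach.

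**Conclusion.** The point holds as a weakness in a stated arrangement, not as a demonstrated bias. The Intervention section allows the coach to take the outcome diet histories of coached participants, and its wording suggests it. Because coaching is confined to one arm of an un-blinded trial, any resulting shift is differential.

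The size cannot be derived from the documents. If the coach assesses all coached participants and this shifts reports by 0.10 to 0.20 SD, the nominal 5% test rejects in about 12% to 32% of trials with no true effect, at 112 completers per arm and ignoring clustering. The rate is lower if the coach assesses only some of them, and there is no excess from this source if the coach is outside the three.

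Only the dietary secondary outcomes are exposed. The primary outcomes are blood pressure readings from an automated device and are not affected. The change is worth making because it is cheap and has to be in place before the follow-up histories are taken.

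**What to change.** State in the Intervention section whether the coaching dietitian is one of the three assessors, and add wording such as:

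*No dietitian takes a six- or twelve-month diet history from participants whom he or she coached. Follow-up assessors are allocated by a rota that gives each an equal share of participants in both arms, within every housing complex where possible. The assessor is recorded for each history.*

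A ban on the coach at follow-up alone could create a new imbalance: coached participants would change assessor from baseline and controls would not. The rule should therefore apply in the same way in both arms, preferably by having the non-coaching dietitians also take the baseline histories. If one of the three coaches everyone, the other two would take all histories in both arms. If each dietitian coaches some groups, a colleague assesses those groups, and any change of assessor since baseline is matched among controls.

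The cost is a rota and one recorded field, with no extra staff. The downside is that the follow-up work may fall on two of the three dietitians, and some participants may change assessor from baseline. If the roles are already separate, a sentence saying so settles the question of overlap.

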### Study tools and measurements

The following tools and measurements will be used to evaluate the effect of the intervention and compliance of the participants regarding lifestyle modification included in the intervention. The measurements will be taken at baseline, six months and twelve months for both groups.

#### Blood pressure measurement

Systolic and diastolic arterial blood pressure will be measured by using Omron Automated Blood Pressure Monitor HEM-7211 which is recommended by the Malaysian Hypertension Association. The arterial blood pressure measurement will be done according to the standardized procedure recommended by World Health Organization [19]. After a rest of ten minutes, two sitting blood pressure will be taken 5 minutes apart on either arm. The average of these two readings will be used as the BP reading of the individual.

#### Questionnaire booklet

A booklet of self-administered questionnaires will be provided for the participants to be completed. Questionnaires include i) Socio-demographic characteristics, ii) Knowledge, awareness and treatment of hypertension, and iii) Global Physical Activity Questionnaire (GPAQ) and, iv) Socio Cognitive variables.

The questionnaire for knowledge, awareness and treatment of hypertension is adapted from the questionnaire developed by World Health Organization [20]. The questionnaire has been translated into Malay version. Face validity has been conducted with 30 participants. The results from the pilot testing showed that contents of the questionnaire are understandable to the participants and can be applied for targeted population.

GPAQ is a tool developed by World Health Organization. It consists of 16 questions to measure the level of physical activity of each individual. The total score of physical activity will be expressed as METs (Metabolic Equivalents). One MET is defined as the energy cost of sitting quietly, and is equivalent to a caloric consumption of 1 kcal/kg/hour. In order to calculate a person's overall energy expenditure, 4 METs will get assigned to the time spent in moderate activities, and 8 METs to the time spent in vigorous activities [21]. The GPAQ questionnaire has been translated and validated into Malay version [22]

#### Dietary assessment

7 Days Diet History is chosen for dietary assessment. The tool has been pre-tested with 20 subjects from the community housing complexes, 10 with hypertension and 10 without hypertension. The 7 Days Diet History will be conducted by trained dietitians. A diet history flip chart will be used as a supplementary tool to assist the study participants during the dietary evaluation and to help in estimating the portion size of the foods consumed [23].

#### Physical evaluation

Height will be measured without socks and shoes by using a calibrated vertical Seca Portable 217 Stadiometer, to the nearest millimetre. Weight will be measured with light clothing using a Seca 813 digital electronic scale, to the nearest decimal fraction of kilogram. Body mass index (BMI) will be calculated as weight in kilograms divided by the square of height in meters. Body fat composition will be measured using a Tanita portable Body Composition Analyzer SC-240 MA. Waist circumference (WC) and hip circumference (HC) will be measured with a non-elastic Seca measuring tape, to the nearest millimetre. Position of waist circumference measurement will be done at a level midway between the lower rib margin and highest point of iliac crest with the tape all around the body in horizontal position [24]. The hip circumference will be measured at the widest point over the buttock yielding the maximum circumference of the buttocks. For women, this is usually at groin level and for men, it is normally about 2-4 inches below the naval/umbilicus.

The "six minute walk test" will be conducted to measure cardiovascular endurance. The six minute walk test is a sub maximal measure of aerobic capacity [25-27]. A calibrated Jamar hand dynamometer will be used to perform the hand grip strength test. Participants will be asked which the dominant hand is. The first test will be performed with dominant hand and then, with non-dominant hand. Three sets of test will be repeated alternatively for both hands [28,29]. The strength of the hand grip will be recorded as kilogram of force.

### Follow up and outcome measurement

The follow up will be at six months and twelve months for both intervention and control groups. The GPAQ questionnaire survey, 7 days diet history, blood pressure measurement and physical evaluation will be conducted at baseline, six months and twelve months. The log book kept by participants in the intervention group will be checked for completeness and errors after one month of the intervention and the record will be taken at three, six, nine and twelve months in order to check the compliance of self-blood pressure monitoring and home-based exercise, and whether they measured their blood pressured once a week or not.

The primary outcomes will be systolic and diastolic blood pressure measured at zero month (enrolment), six months (end of intervention period), and twelve months (maintenance period). Secondary outcome measures include some Social Cognitive Theory variables related to self-efficacy and self-regulatory such as practice of self-blood pressure monitoring, and adherence of exercise. Other secondary outcomes will be dietary intake, level of physical activity and physical fitness in term of both cardio vascular endurance and muscle strength.

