### Sample size calculation and recruitment

The sample size was calculated by assuming p < 0.05 as the significance level, 80% power and 1 to 1 as the ratio of unexposed to expose in sample. The calculation was carried by using the OpenEpi version 2.3.1 [15]. On the assumption of an SD of 15 mmHg and 30% drop out, a sample size of 160 participants per group is required to detect the effect size of systolic blood pressure 5.4 mm Hg. The effect size used to calculate the sample size was based onthe result of a previous similar study[16].

Universal sampling method will be used to recruit the study participants. The 431 residents of the selected community housing complexes who were diagnosed as (stage 1 to 3) hypertension will be invited to the study. We will take all participants which fit with inclusion criteria and willing to participate to the study so that actual participants may be more than calculated sample size.

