### Data management and analysis

The data analysis will be done by using Stata software (version 11: StataCorp). Bivariate analysis such as Chi-square tests (for dichotomous and categorical variables), t test and ANOVA (for continuous and normally distributed variables) and Mann-Whitney-U test (for continuous variable with skewed distribution) will be applied to compare the two groups with respect of socio-demographic characteristics, number of clinic visits, practice of self-blood pressure monitoring, blood pressure at the time of enrolment, dietary intake, level of physical activity and fitness.

The primary outcome, change in systolic and diastolic blood pressure at six months and twelve months will be compared between and within the groups by using t test and ANOVA. If there are some differences in group characteristics, it will be adjusted by performing multivariate analysis of variance (MANOVA).

Since the secondary outcomes such as numbers of self-blood pressure monitoring, dietary intake, body composition (BMI, fat percentage, waist and hip circumference ratio), level of physical activity and physical fitness are also continuous variables, these will be examined as per primary outcome. The normality of the continuous variables will be checked before analysis and proper transformation will be done if the data is not normally distributed. The level of statistical significance will be set at p < 0.05.

In order to calculate nutrient intake, Nutritionist Pro™ Diet Analysis software will be used to analyse the diet record. It will focus mainly on energy, protein, fat, carbohydrate, sodium, dietary fibre and others. Based on the 7 days diet histories, the average energy consumed with macronutrients (e.g: Energy intake (kcal), protein (g), fat (g), saturated fat (g) and others) and micronutrients (e.g: calcium (mg), iron (mg), vitamins and minerals) value will be calculated. All nutrient intakes will be transferred to the Stata software for final data analysis.

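### Four primary blood pressure comparisons share one undivided 0.05 level with no decision rule, while the trial is sized for a single systolic comparison

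*Protocol article*

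**What the plan says.** The section Follow up and outcome measurement of the protocol article states: "The primary outcomes will be systolic and diastolic blood pressure measured at zero month (enrolment), six months (end of intervention period), and twelve months". The Abstract also names both pressures as primary.

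The section Data management and analysis turns this into comparisons: "change in systolic and diastolic blood pressure at six months and twelve months will be compared between and within the groups by using t test", with ANOVA named alongside. The same section gives one threshold for the whole analysis: "The level of statistical significance will be set at p < 0.05".

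The section Sample size calculation and recruitment uses systolic pressure only: "a sample size of 160 participants per group is required to detect the effect size of systolic blood pressure 5.4 mm Hg". The inputs are "The sample size was calculated by assuming p < 0.05 as the significance level", a power of 80% with equal group sizes, and "On the assumption of an SD of 15 mmHg and 30% drop out". It states no diastolic difference, standard deviation or power, and does not say at which visit the 5.4 mmHg is expected.

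Nowhere does the article rank the four comparisons, divide the 0.05 among them, or say how many must reach significance for the trial to count as positive.

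**The concern.** Two pressures at two follow-up visits give four between-group results, each labelled primary. Without a stated rule, a reader of the final report cannot tell whether one significant result out of four was always going to count as success, or whether that was settled once the results were known. The trial is un-blinded, so nothing in the design itself guards against choosing the headline late.

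The planning does not match the analysis either. The sample size was worked out for one systolic test at the full 0.05, while the analysis declares four primary tests. Depending on the rule eventually applied, either the false-positive rate for the primary claim exceeds 5%, or the power for that claim is below 80%.

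**Working it through.** **Inputs from the protocol article.** Difference 5.4 mmHg systolic, SD 15 mmHg, alpha 0.05, power 80%, 1:1 allocation, dropout 30%, 160 per group (Sample size calculation and recruitment). Two pressures and two post-baseline visits (Follow up and outcome measurement; Data management and analysis). Sidedness is not stated. Two-sided is taken because it reproduces the stated size.

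**Step 1: reproduce the stated size.** Evaluable per group: n = 2 × [SD × (z(0.975) + z(0.80)) / difference]² = 2 × [15 × (1.960 + 0.842) / 5.4]² = 121.1, so 122. Adding 30%: 122 × 1.3 = 158.6, so 159, which agrees with the stated 160 apart from rounding. A one-sided test needs 96 evaluable and 96 × 1.3 = 124.8, so 125, which does not agree. The 160 therefore corresponds to one systolic test at two-sided 0.05. (Dividing by 0.7 instead would give 175; how dropout was handled is a separate matter.)

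**Step 2: count the comparisons.** 2 pressures × 2 visits = 4 between-group comparisons. The planned within-group comparisons are not counted here.

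**Step 3: error if any one success counts.** With four independent tests, 1 − 0.95⁴ = 0.185; the upper bound is 4 × 0.05 = 0.20. Independence is not realistic: the two pressures come from the same readings, and both changes start from the same enrolment value. The document gives no correlations, so they are assumed. Simulated four-variate normal test statistics, counting any |z| > 1.96, give:

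| Systolic–diastolic correlation | Between-visit correlation | At least one false positive |
|---|---|---|
| 0.5 | 0.4 | 16.5% |
| 0.5 | 0.5 | 16.2% |
| 0.7 | 0.5 | 14.9% |
| 0.7 | 0.7 | 13.7% |
| 0.8 | 0.7 | 12.8% |

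The range is about 13% to 17%. If the three visits have equal variances and equal correlation r with one another, two changes from a shared baseline have covariance 1 − r and variance 2 − 2r (in units of the common variance), hence correlation 0.5. The two rows with 0.5 between visits then apply, giving about 15% to 16%.

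**Step 4: if all four must succeed.** Type I error is not inflated. Joint power cannot exceed that of the weakest comparison. Systolic power is 80% with 122 evaluable per group, so the joint figure falls below that unless the other three are certain to succeed. It cannot be computed, because the article gives no diastolic effect or SD.

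**Step 5: what dividing alpha would cost.** At 0.05/4 = 0.0125 the systolic test needs 173 evaluable per group, or 173 × 1.3 = 224.9, so 225 by the article's own dropout method, against 160. Holding the size, systolic power is 62% with 122 evaluable and 58% with 112 (160 × 0.7). A fixed testing order leaves the lead test at 0.05, so the size calculation stands as it is.

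**The case against.** The strongest objection is that handling of multiple comparisons is often left to an analysis plan, and that the single 0.05 sentence is a general convention; it does not declare that each of four tests can carry the trial. It is true that testing each comparison at 0.05 is a reading of that sentence together with the t tests, and that a per-test level is not a familywise promise. But the article itself fixes the four primary comparisons, the tests, the one level and a sample size for one of the four. The point rests on what it states.

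ANOVA might be meant as one joint test across visits. The text does not commit to that: t tests are named beside it, and MANOVA is reserved for adjusting group differences.

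The Objectives put the effect during the six-month intervention first and its persistence second, and twelve months is described as a maintenance period. This is a partial ordering and supports the choice of lead visit, but it is not a testing rule.

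Four stronger readings are tempting and are not supported:

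- That enrolment pressure is itself a primary outcome. The list of times includes it, but the analysis section defines the primary outcome as change at six and twelve months and lists enrolment pressure among the variables for comparing the groups.
- That the false-positive rate is 18.5%. That is the independence figure.
- That error is inflated whatever the rule. It is not if all four must succeed.
- That the trial was sized for six months. The calculation names systolic pressure but no visit.

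**Conclusion.** The point holds as a missing decision rule combined with a sample size for one comparison out of four. If any one significant result counts, the chance of at least one false-positive primary result is about 13% to 17%, against the nominal 5%. That range rests on assumed correlations of 0.5 to 0.8 between systolic and diastolic and 0.4 to 0.7 between visits. If all four must succeed, there is no inflation, but power for the primary claim is below 80% by an amount the document does not allow one to calculate. The article does not say which rule applies, and that is the defect. Clustering is a separate issue and is not part of these figures. This should be corrected; the remedy is a change of wording and does not touch the design.

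**What to change.** State, before outcome data are compared between groups, that change in systolic pressure from enrolment to six months is the lead primary comparison, tested at two-sided 0.05. Systolic is the natural choice because the size was computed for it. Six months is chosen because it is the end of the intervention and the effect that the Objectives put first; the sample size section does not settle the visit.

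Then test change in diastolic pressure at six months, systolic at twelve and diastolic at twelve in that order, each at 0.05 and only if the one before is significant. Alternatively, make these three secondary.

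The sample size does not change. The cost is that diastolic and twelve-month pressure lose stand-alone primary status. Under the fixed order, a non-significant result at any step leaves the later ones descriptive, so a sustained effect at twelve months could be claimed formally only after both six-month comparisons succeed. Requiring all four to succeed, or one joint repeated-measures test, would also settle the rule. The first of these would need a diastolic effect and SD to show its power.
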